| SAMPLING  Study sampling and sample sizes:  Our study sampling frame will consist of all (approximately 35) studies being tested in the Reproducibility Project:Cancer Biology. We will categorize the studies based on theoretical and practical features. We will remove studies due to lack of feasibility (e.g. if there is not a clear relevant effect to predict, such as many in vitro studies especially those focused on cell signaling; if maturation date is too far in the future). We will prioritize studies whose results will be published sooner.  We will work with an independent expert to create or edit two to three questions for each study that can be rendered into dichotomized forecasts. In stage 1, participants will forecast all of the first six (all based on mouse models) studies from the cancer reproducibility project plans to publish. Participants will answer two binary elicitations for six events and simplified continuous elicitations for two events.  When mouse survival or tumor growth curves are used, questions will be created around them. When there are no mouse studies, we will shape a question around a study with a quantitative outcome. We plan to conduct a brief pilot to ensure the question types are relatively intuitive. Question formats might vary slightly depending on pilot results.  For the binary elicitation, our questions will take the two^[[2]](#footnote-2)^ of the following general forms:   1. How likely is it that the replication also be significant (at p ≤ .05)? 2. How likely is it that the effect size of the replication will be as large or larger than the original effect size?   For the simplified continuous elicitation (SCE) for the effect size of the specified treatment group, we will use a four question format, based on [9]:  1. What is the lowest effect size you realistically anticipate will be reported for study X?  2. What is the highest effect size you realistically anticipate will be reported for study X?  3. What is your best guess of the effect size you realistically anticipate will be reported for study X?  4. How confident are you (from 0% to 100%) that your estimated interval (lowest to highest) will include the reported effect size from study X?  Investigator sampling and planned strata:  All respondents will be at least 18 years old and will complete an informed consent.  Our primary sample will include two strata:  *a) Independent Experts*: we will create a sample of about 50 to 100 eligible independent international experts by compiling a list of authors from two searchers based on each original study undergoing replication: a) *related article* searches on PubMed and b) articles citing the original report. We will include corresponding authors and anyone who appears at least three times in any single search.  b) Novices: we will recruit a sample of about 50 to 100 medical undergraduate or upper level undergraduate biology majors, graduate students, or postdoctoral fellows at various universities via department mailing lists to participate in our study.  We will aim to include two secondary strata^[[3]](#footnote-3)^:  *c) Originators*: we will contact each co-author on each original research publication for an elicitation.  *d) Replicators*: we will contact each co-author on each replication protocol - only in cases where data collection has not yet been initiated.  Subjects will be approached through email (except non-experts, who may be approached in a class), and administered the questionnaire electronically.  Individuals will be approached up to five times before declaring them as having declined participation.  Sample size:  Our target sample size is as follows:  We will collect forecasts on 3 events in a half hour. We will collect 2 binary forecasts on 6 effects from 6 experiments + simplified continuous forecasts on overall replication rates). We will split the trial sample into two surveys to minimize the number of trials for which participants only have general expertise.  We will target 30 forecasts per participant on 6 events.  We will aim for 150 participants (50X2=100 independent experts + 50 novices) and expect a minimum of 90 (30X2=60 independent experts + 30 novices). |

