| INTERVIEW AND DATA COLLECTION  Interviews will be conducted in 2 stages:   1. Intake interview: in one 30-minute survey presented over the internet (or in person, or by paper and pencil), we will present subjects with a one-page summary sheet describing each replication study (see Appendix 2), as well as a questionnaire (see Appendix 3). Individuals will be approached using appropriate elicitation technique, whereby we first a) describe the goals of the project and how to complete the questionnaire; b) attempt to motivate good performance by explaining how scoring works; c) provide a simple warm up question (asking for a weather forecast); d) elicit replication forecasts; and e) collect additional cognitive and attitudinal measures. The questionnaire will first collect forecasts, then individual difference variables (as applicable), then demographic variables. 2. Forecasts: subjective probabilities on target experiments.    - 1. 2 binary: Significant difference and direction on 3 replication studies      2. 2 @ 4 parameter simplified continuous (best estimate, range, confidence) on overall replication rates.    1. Individual difference variables       1. Actively Open-Minded Thinking[10]       2. Pace of progress of medical research (AKA Medical Boomster-Doomster, adapted from [11])       3. Self-report of expertise for each study       4. Confidence rating of each forecast       5. Time for forecasts       6. Evidence reliance       7. Familiarity with and Anticipated Impact of Reproducibility Project       8. Estimate of perfect replication of effect sizes    2. Demographics:       1. age       2. gender       3. expertise: H index, title/rank (associate professor, full professor, etc.), number of publications, number of citations (all collected from both SCOPUS & Web of Science), nationality/region 3. Post-event Interview: Once results are available, all participants will be approached for posterior and recalled forecasts. We will collect the first set of posterior distributions when the first batch of results is published. Once all data are collected, we participants will be debriefed about study hypotheses and offered an opportunity to learn their forecast skill against the average of their peers. |

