| PRIMARY ANALYSIS  We will calculate the Brier scores of each individual forecaster, and present a distribution. A Brier score is a proper scoring rule – meaning it incentivizes honest reporting of subjective beliefs – which measures the accuracy of a forecast: BS = 1/N $\sum_{i=1}^{N} \left( f_{i}-o_{i} \right)^{2}$ where *f_i_* is a forecast and *o_i_* is a realized outcome for each of i events.[12] We will decompose into calibration = 1/N $\sum_{i=1}^{N} {1/n_{i}\left( f_{i}-\bar{o}_{i} \right)}^{2}$, and discrimination = 1/N $\sum_{i=1}^{N} 1/n_{i}(\bar{o}_{i}\left( 1-\bar{o}_{i} \right))$.[13] We will construct calibration curves for individual forecasters. Our null hypothesis is that mean Brier score 95% confidence intervals exclude Brier score for a matched sample size of hypothetical forecasters predicting same trials using a random number generator. We will also measure the Brier Skill Score for individuals: BSS = 1 – BS/BS_ref_ where BS_ref_ is the base rate for the reference class or of a confidence interval. The sample variance can be used when is BS_ref_ unknown.[14]  Primary endpoint   1. Replicability rate measures: The brier scores for aggregate measures will be slightly higher than .25 (note: .25 is the equivalent of a 50-50 prediction meaning “I don’t know” or a random guess). The mean forecaster will perform slightly worse than base-rates. Forecasts will be skewed toward predicting more successful replications than observed, but less than statistically expected. The order of successful predictions of aggregate replicability rates will be: 2. Effect sizes at least as large (Brier of about .20 to .25) 3. Significance (p-values) (Brier of about .25)   An a priori power analysis suggests we need a sample size of 34 to detect if expert Brier scores are different than a constant (e.g. random guessing (BS = .25) or a base rate (e.g. 80% of significant effects in cancer phase 3 trials favor the new treatment[15]) by a moderate degree (difference from a constant of Cohen’s d = .5) assuming power = .80 and alpha = .05.   1. Individual study measures: The Brier scores for individual studies will be slightly lower than .25. Forecasts will predict more successful replications than observed. Brier scores will be lower (forecasts will be more successful) for forecasting the direction of the difference between effect sizes (Outcome2) compared to forecasting significant differences (Outcome1). Base-rates will outperform the typical forecaster, but aggregating the top-tier of forecasters will beat base-rates. |

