| SECONDARY ANALYSIS ON FORECAST SKILL^[[4]](#footnote-4)^  An a priori power analysis suggests we need a sample size of 34 per group to detect if detect if the experts differ from (d = .5) the novice group assuming power = .80 and alpha = .05, and we need about 180 total respondents to detect a moderate difference (f = .25) between all four strata. As analysis is exploratory, we do not intend to correct for multiple hypothesis testing.   1. Expert strata analysis: 2. The order of predicted replication rates will be: 3. Novices/Non-experts (Should be optimistic since and less attuned to the “replicability crisis” across scientific disciplines) 4. Originators (if available- should be optimistic due to their investment in these results, but more realistic than novices) 5. Independent Experts (Should be less biased due to independence from findings) 6. Replicators (if available- theoretically well attuned to flawed research design and practices) 7. The order of forecast skill will be: 8. Independent Experts (should have sufficient expertise and less biased by own work) 9. Originators (if available- should have sufficient expertise, but more myside bias) 10. Replicators (if available- assumes lab skills are higher than knowledge for this group) 11. Novices/Non-experts (assuming expertise and forecast skill are related, they have the least expertise) 12. The order of variability in forecasts will be: 13. Novices/Non-experts (assuming expertise and forecast skill are related, there should be more variability for those with the least knowledge) 14. Independent Experts 15. Replicators (if available- assumes replicators are well attuned to good and bad study design and difficulty of carrying out certain studies) 16. Originators (if available- assuming expertise and forecast skill are related, there should be less variability in recognizing real empirical relationships and flawed study design by those who have devoted their lives to studying these topics) 17. Expertise will have an inverse U-shaped (∩) relationship with forecasting success. People with low expertise will perform poorly due to inadequate information, and people with high expertise will perform poorly due to maladaptive beliefs (e.g. confirmation bias). The correlation between perceived expertise and Brier score will be ranked as follows:      1. Originators (if available- should perform when they claim higher expertise; have motivation to honestly claim high expertise for some, but not all topics) 2. Independent Experts (may be less discriminating in expertise ratings than originators since they don’t have personal relationships with any of the studies) 3. Replicators (if available) 4. Novices/Non-experts (should have consistently low expertise ratings) 5. Predictors of Forecast Skill: We will test the relationship between each demographic and scale variables and Brier Skill Score, secondarily looking at components of calibration and discrimination. The individual differences should influence the forecasts in the following order (from most to least influential). 6. More extreme updaters: Those who update more extremely relative their will have more accurate forecasts^[[5]](#footnote-5)^. 7. Pace of progress: Those who believe medical technology should progress quickly (slowly) will have more optimistic (pessimistic) forecasts. 8. Evidence reliance: 9. Those who rate the methodology of the replication attempt as important will be pessimistic. 10. Those who cite specific trial outcomes as evidence will be worse forecasters, and those who cite treatment or disease type (base rates) will be better forecasters. 11. Expertise: Those will high (self-reported and actual) expertise will be more accurate; actual expertise (H- & M-indices) will be more predictive of forecasting skill. 12. Confidence will be weakly correlated with forecasting skill. We expect a hard-easy effect where forecasters are overconfident on hard items and underconfident on easy items. 13. Demographics     1. We will also test methods of identifying forecasting skill early (prior to target event realization) the relationship between individual forecaster’s Brier scores and their average squared distance to the median compared to other baselines (mean, expectation due to chance, expectation due to base rates if available) - we hypothesize that this will lead to a strong relationship with forecast skill. 14. Aggregation of Forecasts 1: We will test whether different aggregation approaches give better forecast performance (i.e. lower Brier scores). First, to determine the relative value of using combined forecasts to make decisions, we will construct a curve of showing the relationship between Brier scores and number of aggregated forecasts. Specifically, the curve will reflect n=0 aggregation (i.e. average Brier scores of individual forecasters); n=1 (i.e. average Brier score when two forecasters forecasts are randomly aggregated); n=4 (i.e. average Brier score when 5 randomly selected forecasts are aggregated); and n=9 (i.e. average Brier score when 10 randomly selected forecasts are aggregated). We will also use transformations to make predictions more extreme.[16,17] 15. Predictors and Aggregation: Using individual differences and demographic variables that show low skill identified in step 1, we will test the competitiveness of aggregated low skill forecasters with the individual scores of high skill forecasters. For instance, suppose we find a relationship between high M-index and high forecast skill. We will then test whether, if we combine forecasts from 2, 3, 5 and 10 low M-index forecasters, on average the forecast outperforms the average forecast of high M-index forecasters.   After we have completed forecast scoring, we will also rank all individual forecasters by their Brier skill scores, and randomly select individuals within tiers of upper, middle, and lower thirds. We will test whether combined forecasts of 2, 3, 5 and 10 “low skill” forecasters can, on average, beat the forecast of randomly selected individuals from each skill tier. Brier scores will be used; as well, they will be decomposed into discrimination and calibration. |

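### Skill thirds are cut and compared on the same six outcomes per person; a top tier formed that way can appear to beat base rates by selection alone

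*Protocol*

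**What the plan says.** Protocol, PRIMARY ANALYSIS, under the primary endpoint item on individual study measures: "Base-rates will outperform the typical forecaster, but aggregating the top-tier of forecasters will beat base-rates". The section does not define the top tier.

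Protocol, SECONDARY ANALYSIS ON FORECAST SKILL, closing paragraph, is the only place that forms tiers. "After we have completed forecast scoring", the plan says, "we will also rank all individual forecasters by their Brier skill scores, and randomly select individuals within tiers of upper, middle, and lower thirds". It then asks whether combined forecasts of 2, 3, 5 and 10 low-skill forecasters can "on average, beat the forecast of randomly selected individuals from each skill tier". No held-out studies, cross-validation or null distribution for a selected tier is named.

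Protocol, INTERVIEW AND DATA COLLECTION, gives the information behind each ranking: "2 binary: Significant difference and direction on 3 replication studies", so 2 × 3 = 6 binary forecasts per person.

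Protocol, SAMPLING, Sample size: "We will aim for 150 participants (50X2=100 independent experts + 50 novices"), with an expected minimum of 90. The Survey Versions appendix lists one novice survey, on the version 1 studies. So version 1 has 50 + 50 = 100 people at target and 30 + 30 = 60 at minimum; version 2 has 50 and 30.

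**The concern.** A ranking on six outcomes is largely a ranking on luck. Forecasters whose guesses happened to lean the right way fill the upper third. Averaging their forecasts and scoring the average on the same six outcomes gives that luck back as accuracy. The study could then report a skilled minority that outperforms base rates although every forecaster was equally uninformed. This prediction stands with the primary-endpoint hypotheses, so it could become a headline claim about the research community.

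**Working it through.** **The plan's own figure.** The protocol gives no power or error rate for the top-tier comparison. Its nearest figure, 34 forecasters to detect d = .5 from a constant (power .80, alpha .05), reproduces as a two-sided one-sample t-test: 33.4, rounded up to 34. That figure is not in dispute.

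**Inputs from the protocol.** Three studies × two questions per person; thirds by Brier skill score after scoring; 30 to 100 people per survey version. Since BSS = 1 − BS/BS_ref, ranking by BSS within a version with a common reference is the same as ranking by Brier score.

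**Assumptions, not in the protocol.** Forecasts independent of outcomes (no skill), with SD 25 points in the main case; independent outcomes; success rates as stated below. The aggregate is the mean forecast of the tier.

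**Expected values without selection.** Take forecasts centred on 60% and outcomes at 50%.
- Base rate of 50%: (.5)² = .25.
- Aggregate of many unselected forecasters: .5 × (.4)² + .5 × (.6)² = .08 + .18 = .26.
- Individual: .26 + (.25)² ≈ .32.

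An unselected crowd is therefore slightly worse than the base rate.

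**Simulation, main case.**
- The thirds score about .21 / .32 / .44, although all forecasters are equal. Their average is (.21 + .32 + .44)/3 ≈ .32, as expected.
- At n = 100 the same-data top-third aggregate scores .167 and a random third .261. Selection alone is worth .261 − .167 = .094.
- The top-third aggregate beats the base rate in 98% of runs at n = 30, and in 99% at n = 50 and n = 100. A random third does so in about 40%.
- With leave-one-study-out tiers, top and bottom thirds score .314 and .315, and the top-third aggregate beats the base rate in about 40% of runs. The false advantage is gone.

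**How far the size depends on assumptions.** With forecasts centred on 65% and 30% success, the same-data top third beats the base rate in about 50% of runs, against 22% for a random third. The table uses n = 50 and no skill; optimistic means a beta distribution with mean .7.

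| Forecasts | Success rate | Reference | Same-data top third wins | Leave-one-study-out | Random third |
|---|---|---|---|---|---|
| Uniform | .5 | 50% | 100% | 46% | 44% |
| Centred on base rate | .5 | true rate | 100% | 47% | 45% |
| Optimistic | .8 | 80% | 83% | 34% | 34% |
| Optimistic | .5 | realised rate | 66% | 14% | 12% |
| Optimistic | .2 | realised rate | 12% | 2% | 1% |
| Optimistic | .2 | 80% | 100% | 98% | 99% |

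Two limits can be checked by hand.
- If all outcomes agree and the realised rate is the reference, the reference score is 0 and nothing can beat it.
- If the reference is 80% and 30% succeed, the reference scores .3 × (.2)² + .7 × (.8)² = .012 + .448 = .46. An unselected aggregate at 65% scores .3 × (.35)² + .7 × (.65)² = .037 + .296 = .33. A random third therefore wins too (98% of runs), and selection is not the reason.

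**The tertile analysis.** Here the plan asks whether combined low-skill forecasters beat individuals. In the main case, ten combined bottom-third forecasters beat the mean top-third individual in 0% of runs, although ten randomly chosen forecasters beat the mean individual in 96%. Same-data selection handicaps the low tier and flatters the upper one.

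**The case against.** Five points can be made for the plan.

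1. **The link between the two sections is inferred.** The thirds belong to a different analysis, and a statistical analysis plan not shown here might define the top tier otherwise. This stands, so the point is conditional for the primary-endpoint prediction. The protocol does mention an outcome-free idea, distance to the median, but tests it as a predictor of skill and does not use it to form tiers. For the thirds themselves the reuse is explicit.

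2. **The secondary analyses are called exploratory, and footnote 4 says some cannot be done.** That tempers the tertile analysis. It does not cover the prediction placed under the primary endpoint. That prediction has no stated test, so the remedy concerns what may be concluded from it.

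3. **A reader might infer that a top tier beats base rates in every case.** The table does not support this. Selection raises the chance in every simulated row, but the level runs from 12% to 100%, and the protocol itself expects optimistic forecasts.

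4. **A reader might also infer that trait-based groups differ by construction**, because the plan proceeds by "Using individual differences and demographic variables that show low skill identified in step 1". The documents do not support this. Traits are measured independently of the outcomes; choosing among them is a weaker mechanism than ranking people on outcomes, and no calculation here covers it.

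5. **Leave-one-study-out is not a complete cure.** Under no skill the held-out tier still beats the base rate in about 40% of runs in the main case. Footnote 4 reports little variability in the replication results. If every replication failed and people differed only in general optimism (assumed mean 60%, person-level SD 15-20 points, total SD 25), leave-one-study-out top tiers would beat a 50% reference in 90-100% of runs, against 0% for a random third, without any ability to tell studies apart. This stands and shapes the fix.

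**Conclusion.** The concern holds in a conditional form. The secondary analysis cuts thirds after scoring and compares them on the same six outcomes per person. The primary-endpoint prediction offers no other way to form its top tier. If it is formed this way, zero-skill forecasters centred on 60% with outcomes at 50% give a winning top tier in about 98-99% of runs, against about 40% for a random third; with 65% forecasts and 30% success it is about 50% against 22%. These figures rest on assumed forecast distributions, independent outcomes and the true rate as reference. A win over base rates would therefore not by itself be evidence of a skilled minority.

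The tertile comparison with upper-tier individuals is also uninterpretable, but the bias runs against combined low-skill forecasters, so a null result there would mean little. It would be wrong to say that the top tier must win, that the protocol expressly defines the top tier by these outcomes, or that trait-selected groups are bound to differ.

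**What to change.** Define the top tier. Rank forecasters within survey version on two of their three studies, score the tier on the third only, and rotate so that each study is held out once. Tune any extremising parameter the same way, and use the same tiers for the low-skill comparison. State the base-rate reference.

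Judge the top-tier aggregate against a permutation or random-tier null, because falling below the base rate is not enough on its own. If nearly all outcomes agree, say that a tier can win through general optimism or pessimism alone. Permuting the three study labels within a version gives 3! = 6 arrangements, or 6 × 6 = 36 over both versions, so that null is coarse.

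If this is not adopted, label the tier results descriptive and do not conclude that a skilled top tier beats base rates.

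No new data are needed. The cost is a little more analysis, and tiers that are noisier because they rest on two studies per person.

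### The 34 per group given for the expert-versus-novice comparison is the one-sample figure; a two-sample test at d = 0.5 needs 64 per group (two-sided), and 34 per group gives about 53% power

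*Protocol*

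**What the plan says.** The Protocol makes three a priori power statements.

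- Primary Analysis, for experts against a fixed reference value: "we need a sample size of 34 to detect if expert Brier scores are different than a constant", with "difference from a constant of Cohen’s d = .5) assuming power = .80 and alpha = .05".
- Secondary Analysis on Forecast Skill, for experts against novices: "we need a sample size of 34 per group to detect if detect if the experts differ from (d = .5) the novice group", with the same d of 0.5, power of 0.80 and alpha of 0.05.
- The same sentence, for all four strata: "we need about 180 total respondents to detect a moderate difference (f = .25) between all four strata".

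The Sampling section, under Sample size, sets a target of 150 participants (100 independent experts and 50 novices) and says the team will "expect a minimum of 90 (30X2=60 independent experts + 30 novices" in brackets. Neither power statement on d = 0.5 says whether the test is one- or two-sided. The secondary section describes its analyses as exploratory. The Survey Versions list in the Protocol Appendix shows two expert study sets but only one novice survey, covering studies 15, 21 and 44.

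**The concern.** The same number, 34, serves two different designs with identical d, power and alpha. In one design a single group is compared with a known constant. In the other, two independent groups are compared, and both means carry sampling error. For the same standardised difference the second design needs roughly twice as many people per group, so both statements cannot be right.

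What is at stake is how the planned sample is judged. Set beside a stated need of 34 per group, the expected minimum of 30 novices looks like a near miss, and 60 experts look ample. Set beside the correct requirement, the minimum sample is clearly short of 80% power.

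**Working it through.** **Inputs.** d = 0.5, power 0.80, alpha 0.05 (Primary Analysis and Secondary Analysis on Forecast Skill); 100 v 50 at target and 60 v 30 at minimum (Sampling, Sample size). Two-sided testing is an assumption, checked in step 1. All final figures use the noncentral t distribution.

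**1. Reproduce the primary figure (one sample).** The normal approximation is n = (1.960 + 0.842)² / d² = 7.85 / 0.25 = 31.4. The t-test adds about two: n = 33.4, rounded up to 34, with power 0.808 at 34. The one-sided version gives 26.1, so 27. The Protocol's 34 is therefore correct, and it shows that the authors were working two-sided.

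**2. Try to reproduce the two-group figure.** The normal approximation is n per group = 2 × 7.85 / 0.25 = 62.8, so 63. The exact results with equal groups are:

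| Test | n per group for 80% power |
| --- | --- |
| Two-sample, two-sided | 63.8 → 64 |
| Two-sample, one-sided | 50.2 → 51 |

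Neither gives 34. With two experts per novice, as recruitment plans, the smaller group alone would need 48 (two-sided) or 38 (one-sided).

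**3. Power that 34 per group delivers.** The noncentrality is d × √(n₁n₂/(n₁+n₂)) = 0.5 × √(34 × 34 / 68) = 0.5 × √17 = 2.06, on 66 degrees of freedom. Power is 0.529 two-sided and 0.654 one-sided. For 80% power, two-sided, at 34 per group the difference would have to be about d = 0.69.

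**4. Power at the sample sizes in the Sampling section, two-sided, all experts pooled.**

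| Experts v novices | Noncentrality | Power at d = 0.5 | Detectable d at 80% power |
| --- | --- | --- | --- |
| 100 v 50 (target) | 0.5 × √(5000/150) = 2.89 | 0.82 | 0.49 |
| 60 v 30 (minimum) | 0.5 × √(1800/90) = 2.24 | 0.60 | 0.63 |

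**5. The same, under a labelled assumption.** Suppose the comparison were restricted to the studies that novices answered. Only the experts given survey 1 would then count, which is half of them:

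| Experts v novices | Noncentrality | Power at d = 0.5 | Detectable d at 80% power |
| --- | --- | --- | --- |
| 50 v 50 (target) | 0.5 × √25 = 2.50 | 0.70 | 0.57 |
| 30 v 30 (minimum) | 0.5 × √15 = 1.94 | 0.48 | 0.74 |

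One-sided, these two powers would be 0.80 and 0.61.

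**6. Cross-check on the third statement.** A four-group analysis of variance at f = 0.25 needs 178.4 in total, which agrees with about 180. Two of the three power statements thus reproduce with standard methods, and only the two-group one does not.

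**The case against.** The strongest reply is that nobody plans to recruit 34 v 34. The target of 100 v 50 gives 0.82, so the design at full recruitment reaches the power the Protocol claims, even though the printed requirement is wrong. This stands, and it means that the 53% describes the stated figure and not the planned study.

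The comparison is also secondary and exploratory. The primary statement is correct, and 60 to 100 experts exceed the 34 it asks for. This too stands. It limits the weight of the error without making the number right.

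Sidedness is not stated, and the Protocol predicts a direction (independent experts first in skill, novices last). A one-sided test would still need 51 per group, so it does not rescue 34. It would, however, lift the figures in steps 4 and 5, so the correction must name the sidedness it uses.

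A reader might infer more than the document supports:

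- *That the comparison as planned has only a coin-flip chance of success.* This holds for 34 v 34, and for 30 v 30 if the analysis is restricted to the shared studies. No passage makes that restriction. The overall replication rates that the questionnaire also elicits do not depend on which studies a respondent saw, so all experts could be used there.
- *That a null result will be reported as showing no value in expertise.* Nothing in the Protocol says so.
- *That the four-stratum figure of about 180 is also wrong.* It is arithmetically correct. Footnotes 3 and 4 already disclose that two strata were not pursued and that some analyses fall away as a result.

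**Conclusion.** The stated requirement is wrong as written. For "the experts differ from (d = .5) the novice group" at power 0.80 and alpha 0.05, a two-sided two-sample t-test with equal groups needs 64 per group, not 34; the one-sided requirement is 51. At 34 per group the power is about 53% (65% one-sided). The figure coincides exactly with the one-sample result under Primary Analysis. Carry-over is the likely explanation, although the document does not say how the figure arose.

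For the study as planned, with experts pooled and a two-sided test, power is adequate at target (0.82) and short at the expected minimum (0.60). The two-sided reading is an assumption, supported by the fact that only a two-sided test reproduces the primary 34. The survey-1-only figures rest on a further assumption about the analysis set. This is a correction to a stated figure for an exploratory secondary comparison. It does not threaten the primary analysis.

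**What to change.** In Secondary Analysis on Forecast Skill, replace 34 per group by 64 per group, and say that this is for a two-sided two-sample t-test with equal group sizes. Add the power at the sample sizes in the Sampling section with all experts pooled: 0.82 at 100 v 50 and 0.60 at 60 v 30 (detectable d at 80% power about 0.49 and 0.63).

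If the authors intend to compare the groups only on the studies that novices answered, they should say so and give 0.70 at 50 v 50 and 0.48 at 30 v 30 instead. Otherwise those figures should appear, if at all, only as a labelled assumption. The statement of about 180 respondents can stay.

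The cost is wording only. No participants are added and no analysis changes, but the power stated for the minimum sample becomes less favourable.
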